### Exclusion Criteria

Participants will be excluded if they (1) sustained a concussion or lower extremity injury in the last 3 months, (2) have any neurological conditions (ie, epilepsy) or are on any medications that affect the central nervous system, (3) had concomitant surgeries at the time of their index ACLR (eg, MCL repair), (4) are still actively participating in rehabilitation, or (5) are unable to attend intervention sessions 3 times per week.

### Randomization and Blinding

Participants will be randomized into either the VRMM+NTR group or the VR sham+NTR group, following the completion of preassessment outcome measurements (Table 1). A block randomization scheme will be used, and blocks ranging from 2 to 6 will be generated using an online randomization generator (allocation ratio 1:1). Group allocations will be sequentially numbered and sealed in opaque envelopes by a third-party individual not associated with the study. Interventionists, outcome assessors, and participants will be blinded to group allocation. After the collection of preassessment outcomes and prior to session 1, participants will be randomly assigned to their study condition (ie, VRMM+NTR group or VR sham+NTR group).

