## Methods

### Study Design

A double-blinded, 2-arm feasibility trial will be conducted to investigate a VRMM intervention. To address aim 1, recruitment, retention, adherence, and acceptability outcomes will be collected throughout the trial. To address aim 2, changes in injury-related fear and jump-landing biomechanics will be compared between participants randomized to VRMM+neuromuscular training rehabilitation (NTR) or VR sham+NTR. The study schedule is outlined in Table 1.

**Table 1. T1:** Schedule of events for the trial.

	Screening	Preassessment (wk 1)	Week 1 (3 visits)	Week 2 (3 visits)	Week 3 (3 visits)	Week 4 (3 visits)	Week 5 (3 visits)	Week 6 (3 visits)	Week 7 (3 visits)	Week 8 (3 visits)	Postassessment (wk 8)
Review eligibility	✓										
Informed consent		✓									
Demographics		✓									✓
Clinical history		✓									
Height and weight		✓									✓
Knee-related questionnaires IKDC^a^ Tegner ACL-RSI^b^		✓									✓
Injury-related fear (TSK-11)^c^	✓	✓									✓
Jump-landing biomechanics (LESS-RT)^d^	✓										
Jump-landing biomechanics (motion capture)		✓									✓
Adherence log			✓	✓	✓	✓	✓	✓	✓	✓	
Acceptability survey											✓
Randomization		✓									
Control and experimental intervention (neuromuscular training and virtual reality)			✓	✓	✓	✓	✓	✓	✓	✓	
Adverse event reporting		✓	✓	✓	✓	✓	✓	✓	✓	✓	✓

a IKDC: International Knee Documentation Committee.

b ACL-RSI: anterior cruciate ligament–return to sport after injury scale.

c TSK-11: 11-Item Tampa Scale of Kinesiophobia.

d LESS-RT: Landing Error Scoring System-Real Time.

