#### The VRMM Intervention

Participants randomized to the intervention group will undergo an 8-week VRMM intervention (3 times per week, 10-min sessions) in addition to the NTR program. VRMM engages visual and auditory senses to enhance the mindfulness experience and has been successfully used to address chronic pain [38] and anxiety [28,39]. The VRMM intervention will be administered with a commercially available wireless headset (MetaQuest, Meta Platform, Inc) using the Headspace XR application (Headspace, Inc). Prior to the first VRMM session, participants randomized into the VRMM+NTR group will watch a 10-minute educational video on the VR headset detailing the benefits of mindfulness. This will allow the participant to also gain exposure to the feel of the VR headset prior to the implementation of the intervention.

Participants enrolled in the VRMM group will complete a guided mindfulness experience that encourages observation, acceptance, and being present in their current environment through breath awareness. Participants will have the opportunity to complete a variety of mindfulness activities through the Headspace XR application, including focused attention mindfulness (eg, meditation and breath control) and mindful movement. While not directly associated with knee-specific activity, mindfulness was selected because individuals after ACLR must learn how to acknowledge their feelings while maintaining relaxation in specific environmental situations, rather than avoiding stressful situations or difficult emotions. Participants will also engage in mindful movement while in the headset to encourage mindfulness during the integration of movement. Engaging in mindfulness can be beneficial for retraining attentional control systems.

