#### VR Sham

Participants randomized to the sham group will undergo an 8-week VR sham (3 times per week, 10-min sessions) in addition to the NTR program. Participants in the sham group will be able to select and immerse themselves in VR environments (eg, beach and forest) using a medical-grade, wireless system (Limbix Health, Inc). However, participants in the sham group will not participate in any guided mindfulness meditation or mindful movement activities. While the sham environment may promote relaxation, these participants will not learn the mindfulness skills and techniques cultivated through the Headspace XR activities. Therefore, this group will receive an appropriately designed sham intervention by mimicking the experimental intervention as closely as possible, excluding only the active therapeutic element. It is hypothesized that without exposure to specific mindfulness tools, participants in the sham group will exhibit higher levels of injury-related fear and worse jump-landing biomechanics at the end of the study compared to the intervention group. Each VR sham session is 10 minutes in length.

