### Treatment Fidelity

To ensure treatment fidelity, all interventionists will follow standard operating procedures that detail the VRMM+NTR procedures and the VR sham+NTR procedures, including the frequency, intensity, and duration of all activities. Additionally, prior to working with participants, all interventionists will undergo training to ensure that they are safely and effectively implementing the intervention and sham. Throughout the intervention, all interventionists will complete an adherence checklist to describe completed activities during each session. Finally, quality control checks will occur to identify issues as they arise and to maintain consistency of the intervention/sham delivery over time.

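### Interventionists are declared blinded although their duties reveal the arm, and the sham lacks the video on the benefits of mindfulness

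*Protocol article*

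**What the plan says.** All references are to the protocol article.

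- **The claim.** Study Design opens with "A double-blinded, 2-arm feasibility trial will be conducted to investigate a VRMM intervention", and the Abstract uses the same label. Randomization and Blinding specifies who is meant: "Interventionists, outcome assessors, and participants will be blinded to group allocation". Ethical Considerations reserves intentional unblinding for participant safety after a serious adverse event. The Discussion (Rationale and Principal Findings) describes the study as having a low risk of bias.
- **Delivery in the VRMM arm.** The intervention is "administered with a commercially available wireless headset (MetaQuest, Meta Platform, Inc) using the Headspace XR application (Headspace, Inc". Activities run in a fixed order (Table 3), and at least one involves moving the whole body in the headset (Table 4, Energy boost).
- **Delivery in the sham arm.** Participants choose scenes "using a medical-grade, wireless system (Limbix Health, Inc", and "participants in the sham group will not participate in any guided mindfulness meditation or mindful movement activities".
- **Staff duties.** Treatment Fidelity gives interventionists operating procedures covering both arms and adds that "all interventionists will complete an adherence checklist to describe completed activities during each session". Feasibility (Aim 1) has them track adherence to the VRMM component, and records which kinds of mindfulness session were done and how many.
- **The video.** Before session 1, "participants randomized into the VRMM+NTR group will watch a 10-minute educational video on the VR headset detailing the benefits of mindfulness". The same paragraph says this also accustoms the participant to the headset. VR Sham describes no counterpart, yet says the sham works by "mimicking the experimental intervention as closely as possible, excluding only the active therapeutic element".

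**The concern.** There are two linked problems.

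First, the article affirms a design property that its own delivery text rules out. This is not a detail left to a fuller document. The blinding of interventionists is stated outright, and the low-risk-of-bias description leans on it. A published report repeating the statement would credit the trial with a protection it does not have.

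Second, the contrast between arms is meant to isolate mindfulness skills. If only one arm is told beforehand that its VR content is beneficial, and only that arm gets a headset introduction, any difference in a self-reported outcome mixes skill learning with raised expectation. The TSK-11 (aim 2a) is rated by the participant, so a blinded assessor cannot protect it. The acceptability survey is also self-rated, and the article hypothesises that it will favour VRMM. Both matter beyond this trial: the Discussion makes progression depend on the acceptability hypothesis being supported and on a promising aim 2 effect, with partial η² of at least 0.09 as its example.

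**Working it through.** The plan gives no figure on this point, so the check sets the sections side by side.

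**Step 1. Can an interventionist be unaware of the arm?**

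1. The VRMM Intervention and VR Sham name different products for the two arms. Whoever sets up the session has to pick one.
2. The content differs in kind: guided activities in a fixed sequence, some with movement, against a self-chosen scene with no guidance.
3. Treatment Fidelity has all interventionists work to procedures that spell out both arms. Carrying them out correctly requires knowing which arm applies.
4. The checklist (Treatment Fidelity) and the adherence record (Feasibility (Aim 1)) require a description of what was done at each session, including the kind of mindfulness activity. A sham participant has none to record.
5. No section describes a step that would hide any of this, such as separate staff for VR set-up or coded devices. The checklist duty falls on all interventionists, so a division of labour cannot be assumed.

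Items 3 and 4 are sufficient on their own. The conclusion does not depend on how the headsets look.

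**Step 2. Does the sham omit only the active element?**

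1. The section on the VRMM intervention defines the active ingredient as learning mindfulness skills: attention, present-moment awareness, breathing and mindful movement.
2. The video presents the benefits of mindfulness and introduces the headset. Neither is a skill in that list.
3. VR Sham describes no matching video.

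As described, the arms therefore differ in benefit messaging and headset familiarisation as well as in skills training.

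**Step 3. Which blinding claims survive?**

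| Party | Supported by the text? |
|---|---|
| Interventionists | No; contradicted by their duties |
| Outcome assessors | Not contradicted, provided they are not also interventionists |
| Participants | Undermined by the one-arm video and overt mindfulness content, but not disproved |

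**Step 4. How much of the trial can still be corrected?** The planned total is 48 (Sample Size Estimation and Study Population), and 12 had been randomised (Results). 48 − 12 = 36, and 36/48 = 75% of the planned sample.

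**The case against.** The strongest reply is that a trial with blinded participants and assessors is commonly called double-blind, so the label could survive once interventionists are removed from the list. Participants know what they see in the headset, but may not know which VR condition is expected to work. The consent text is not available, so what they are told cannot be judged. This stands: the documents do not show that participant or assessor blinding fails. It does not rescue the sentence that names interventionists.

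It can also be argued that the video belongs to the intervention package and that a matched sham video is a design preference. That is fair as far as it goes. However, the article itself says the sham leaves out the active element alone, and its definition of that element does not include education about benefit.

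Finally, this is a stage 1 feasibility study. The Limitations disclaim firm conclusions on effectiveness, and aim 2b is measured by motion capture. This lowers the stakes without removing them, because progression still uses acceptability and the aim 2 effect size.

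A reader might infer more in three places, and the documents do not support it:

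- **Interventionists collect the TSK-11.** The section on injury-related fear lists weeks 2, 4 and 6 but does not say who administers the scale. With two time levels, the 2×2 analysis apparently does not use those weeks.
- **Blocks of 2 make allocation predictable.** Block sizes vary from 2 to 6 and the envelopes are opaque and prepared by an outside party. Prediction would require knowing a block's size and starting point.
- **The headsets look different.** This is inferred from product names; their appearance is not described.

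**Conclusion.** The point holds in two parts. The statement that interventionists are blinded is contradicted by the article's own account of their work; this is a definite inconsistency that needs no assumption. The sham as described differs from VRMM by more than the active element, which leaves the self-reported TSK-11 and the acceptability survey open to expectancy. This part rests on there being no sham video, and none is described.

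No numerical size is given. A reader might want a figure for the inflation of false-positive findings, but it would depend entirely on an assumed expectancy shift, for which the documents offer no basis. Nor do the documents support concluding that blinding fails altogether: that of participants is weakened and that of assessors is uncontradicted. The correction should be made, since it is cheap and bears on what the trial can claim.

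**What to change.** 1. In Randomization and Blinding, state that interventionists are not blinded. Limit the claim to outcome assessors and to participants being unaware of which VR condition is hypothesised to be active.
2. Qualify the double-blinded label in the Abstract and Study Design, and the low-risk-of-bias description in the Discussion, to match.
3. Give future sham participants a neutral video of equal length (10 minutes) in their headset before session 1.
4. Have participants complete the TSK-11 themselves, away from interventionists.
5. Optionally, add one question at postassessment asking participants which arm they think they were in.

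The cost is protocol wording, one short neutral video and, if wanted, one survey item. The small downside is that the 12 participants already randomised followed the existing procedure, so the date of the change must be reported. No change to the block sizes is needed.

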### Intervention and Sham Groups

#### Neuromuscular Training Rehabilitation

Both groups will complete a previously established, evidence-based late-phase progressive 8-week NTR (Table 2) [10]. This program is designed to address significant functional and neuromuscular limitations that are associated with ACL reinjury risk [10]. Four phases (2 weeks per phase; 3 times per week) will be used to appropriately progress participants through the program. Participants will be progressed through the following exercises: single-leg anterior bounding, lunges, lateral jumps, side planks, prone planks, posterior chain glute bridge, single-leg deadlifts, single-limb hop to stabilization, and single-leg stance (Table 2). These exercises do not directly address jump-landing biomechanics.

**Table 2. T2:** Neuromuscular training rehabilitation (NTR) 8-week exercise progressions^a^.

Progression category	Phase 1 (Week 1 and 2)	Phase 2 (Week 3 and 4)	Phase 3 (Week 5 and 6)	Phase 4 (Week 7 and 8)
Single-leg anterior bounding	Double-leg takeoff to single-leg landing	Double-leg takeoff to single-leg bound	Single-leg takeoff to single-leg landing	Single-leg takeoff to single-leg bound
Rx^b^	3×10	3×10	3×10	3×10
Lunge	Static lunge	Dynamic lunge	Dynamic lunge with weight	Dynamic lunge with weight and trunk twist
Rx	3×10	2×30 feet	2×30 feet	20×30 feet
Lateral jump	Double-leg, noncontinuous	Double-leg, continuous	Single-leg, noncontinuous	Single-leg, continuous
Rx	2×10	2×10	2×10	2×10
Side plank	Bottom knee flexed	Bottom knee flexed+hip abduction	Legs extended	Legs extended+hip abduction
Rx	10×10 s	3×10	10×10–20 s	3×10
Prone plank	Forearms and knees	Hands and toes	Forearm and toes	Forearm and toes+leg lifts
Rx	10×10 s	10×10–30 s	10×10–30 s	3×10
Posterior chain glute bridge	Double-leg glute bridge on Bosu ball	Double-leg glute bridge on Bosu ball with leg extension	Double-leg glute bridge+roll out on the exercise ball	Double-leg glute bridge+leg lifts on the exercise ball
Rx	10×10 s	3×15	10×10 s	3×15
Single-leg deadlift	Flat surface, body weight	Flat surface with weight	Unstable surface, body weight	Unstable surface with weight
Rx	3×10	3×10	3×10	3×10
Single-limb hop to stabilization	18″ hop, arms out	18″ hop, hands on hips	27″ hop, arms out	27″ hop, hands on hips
Rx	10 A/P^c^, 10 M/L^d^	10 A/P, 10 M/L	1×10	1×10
Balance series	Tandem stance, eyes closed, arms across chest, firm surface	Single-leg stance, eyes closed, arms across chest, firm surface	Tandem stance, eyes closed, arms across chest, unstable surface	Single-leg stance, eyes closed, arms across chest, unstable surface
Rx	3×30 s	3×30 s	3×30 s	3×30 s

a For exercises involving a single-limb movement, the repetitions are for each side (ie, 3×15 double-leg bridge+leg lift on the ball would require 3 sets of 15 leg lifts on each side (30 in total).

b Rx: exercise prescription, displayed as sets×repetitions/duration.

c A/P: anterior/posterior.

d M/L: medial/lateral.

#### The VRMM Intervention

Participants randomized to the intervention group will undergo an 8-week VRMM intervention (3 times per week, 10-min sessions) in addition to the NTR program. VRMM engages visual and auditory senses to enhance the mindfulness experience and has been successfully used to address chronic pain [38] and anxiety [28,39]. The VRMM intervention will be administered with a commercially available wireless headset (MetaQuest, Meta Platform, Inc) using the Headspace XR application (Headspace, Inc). Prior to the first VRMM session, participants randomized into the VRMM+NTR group will watch a 10-minute educational video on the VR headset detailing the benefits of mindfulness. This will allow the participant to also gain exposure to the feel of the VR headset prior to the implementation of the intervention.

Participants enrolled in the VRMM group will complete a guided mindfulness experience that encourages observation, acceptance, and being present in their current environment through breath awareness. Participants will have the opportunity to complete a variety of mindfulness activities through the Headspace XR application, including focused attention mindfulness (eg, meditation and breath control) and mindful movement. While not directly associated with knee-specific activity, mindfulness was selected because individuals after ACLR must learn how to acknowledge their feelings while maintaining relaxation in specific environmental situations, rather than avoiding stressful situations or difficult emotions. Participants will also engage in mindful movement while in the headset to encourage mindfulness during the integration of movement. Engaging in mindfulness can be beneficial for retraining attentional control systems.

The Headspace XR application organizes its contents into three broad categories to align with different mindfulness goals and experiences. *Reflect* encourages present-moment awareness, introspection, and mental clarity. Tasks in this category will encourage the identification of current moods and reflection on current thoughts and feelings. *Unwind* promotes mind-body exercises aimed at releasing tension and enhancing breath awareness, such as diaphragmatic breathing. *Play* encourages mindfulness through movement and playful interactions to foster a mindful presence during activities. Across the duration of the 8-week intervention, participants will be advanced in their mindfulness practice to improve skills, such as focused attention and breathing awareness techniques (Table 3). Participants will complete the same, fixed-order combination of reflect, unwind, and play mindfulness activities throughout the 8-week intervention. Each full VRMM session is 10 minutes in length. Descriptions of included Headspace XR activities are presented in Table 4.

**Table 3. T3:** Mindfulness intervention using MetaQuest virtual reality headset and Headspace XR application.

Weeks, session, and activity type	Name	Minutes (total=10 min)
1, 3, 5, 7		
1		
Reflect (mindfulness)	Mood stream	1
Unwind (mindfulness and mindful breathing)	Body scan	5
Play (mindful movement)	Focus slingshot	2
Reflect (mindfulness)	Take a beat meditation	2
2		
Reflect (mindfulness)	Mood stream	1
Unwind (mindfulness and mindful breathing)	Box breathing	2
Play (mindful movement)	Energy boost	5
Reflect (mindfulness)	Take a beat meditation	2
3		
Reflect (mindfulness)	Mood stream	1
Unwind (mindfulness and mindful breathing)	Kindness bubbles	5
Play (mindful movement)	Focus hoops	2
Reflect (mindfulness)	Take a beat meditation	2
2, 4, 6, 8		
1		
Reflect (mindfulness)	Mood stream	1
Unwind (mindfulness and mindful breathing)	Backward counting	5
Play (mindful movement)	Focus slingshot	2
Reflect (mindfulness)	Take a beat meditation	2
2		
Reflect (mindfulness)	Mood stream	1
Unwind (mindfulness and mindful breathing)	Body scan	5
Play (mindful movement)	Focus hoops	2
Reflect (mindfulness)	Take a beat meditation	2
3		
Reflect (mindfulness)	Mood stream	1
Unwind (mindfulness and mindful breathing)	Breathing slingshot	2
Play (mindful movement)	Energy boost	5
Reflect (mindfulness)	Take a beat meditation	2

**Table 4. T4:** Headspace XR mindfulness activities description.

Activity name	Description
Mood stream	Players select daily mood and reflect on that emotion.
Body scan	A foundational full-body scan to notice sensations and reduce stress.
Focus slingshot	Players pay attention to timing to release the slingshot and paint a wall.
Take a beat meditation	Meditation based on selected mood.
Box breathing	Inhale 4 s, hold 4 s, exhale 4 s, hold 4 s guided by a visual.
Energy boost	Players collect orbs and stars through full-body movement.
Kindness bubbles	Players grab hearts representing positive feelings and pop bubbles to release negative ones.
Focus hoops	Players follow flashing hoops in sequence and shoot accordingly.
Backward counting	Players count backward while gently noticing distraction.
Breathing slingshot	Slingshot release timed with inhale and exhale.

The active ingredient of this intervention for participants is learning specific mindfulness skills and tools including focused attention, present-moment awareness, breathing skills, and mindful movement. It is hypothesized that these skills will provide participants with tools to overcome fearful situations, resulting in lower injury-related fear and improved jump-landing biomechanics following the intervention compared to the sham group.

